### Safety and Termination Criteria

Medical staff and researchers will be on-site for continuous monitoring to ensure participants’ safety throughout the exercise protocol. ICU-CARE CPET will be terminated if participants meet the formal criteria as outlined in the standard ATS/ACCP guidelines [17], which include chest pain suggestive of ischemia, ischemic ECG changes, complex ectopy, second- or third-degree heart block, a fall in systolic pressure by 20 mm Hg from the highest value during the test, hypertension (250 mm Hg systolic, 120 mm Hg diastolic), severe desaturation (indicated by pulse oximetry, arterial oxygen saturation [Sp_O2_] 80% with symptoms of severe hypoxemia), sudden pallor, loss of coordination, mental confusion, dizziness or presyncope, and signs of respiratory failure [17]. The test will also be terminated immediately if participants request to stop (volitional exhaustion) or if they exhibit any of the following: significant discomfort preventing continued exercise, abnormal pain, shortness of breath limiting exercise continuation, light-headedness, dizziness, or inability to maintain 60 rpm (revolutions per minute) cadence (±10 rpm).

### Data Monitoring Committee

The research staff will report details and deviations of the data collection process and subsequent analyses to the local research ethics board. Because this is a small observational study, we are not planning an interim analysis, nor will there be a formal data monitoring committee outside of the research team.

### ICU-CARE CPET Protocol

The ICU-CARE CPET protocol (Figure 2) will combine measurements of $\dot{V}O_{2peak}\dot{,V}O_{2}$ on/off kinetics, as previously described by our research team in healthy participants [28], with the addition of two adaptations for ICU survivors. Before the start of this protocol, participants’ seat height and handle angle will be adjusted for comfort. The protocol will be composed of a baseline phase, a CWR phase (on-kinetics), an incremental phase (peak), and a recovery phase (off-kinetics), as described below.

**Figure 2. F2:**
[figure not shown]
Illustration of the ICU-CARE CPET protocol for ICU survivors using an upright cycle ergometer. Orange words represent the protocol adaptations from Santana et al [28] study in healthy controls. CPET: cardiopulmonary exercise test; CWR: constant work rate; ICU: intensive care unit; ICU-CARE: intensive care unit combined assessment of cardiorespiratory exercise; V̇O_2peak_: peak oxygen uptake; V̇O_2reserve_: oxygen uptake reserve. Created in BioRender.

#### Rest Phase

The rest phase consists of 3 minutes baseline, seated on the upright cycle ergometer without pedaling to establish baseline values for $\dot{V}O_{2}$ and NIRS signals prior to initiating the CWR phase.

#### Constant Work Rate Phase (On-Kinetics)

The CWR phase will entail a 5-minute steady-state moderate-intensity upright cycling exercise at the desired intensity of 30%, relative to the individual’s estimated $\dot{V}O_{2reserve}$ (as described below in the .$\overset{˙}{\;V}O_{2reserve}$Calculation section) to perform exercise, with a cadence of 60 rpm [28]. In a recent publication, our team used a 4-step process to standardize and determine the optimal CWR exercise intensity during a CPET protocol [28]. We will adopt and adapt these steps to derive a CWR intensity for ICU survivors, as outlined below.

##### ICU Survivor Prediction Equation for$\dot{V}O_{2peak}$

In this first step, to determine CWR, a recent Canadian adult (≥40 years of age) normative (50th percentile) and sex-specific equation (Equation 1) [54] will be used to predict $\dot{V}O_{2peak}$. Subsequently, an ICU correction factor of 0.75 (ICU0.75) is to be multiplied based on an average of 25% $\dot{V}O_{2peak}$ reduction in ICU survivors, previously described in the literature [5,7,21].

(1)
$$\begin{array}{rl} \text{Estimated }\dot{V}O_{2\text{peak}} & =(\left(0.012905699\cdot H)+(0.007291081\cdot BM\right)\\ \;+(0.564188602\cdot S)-(0.016521850\cdot A)\\ \;-0.076072067)\times ICU0.75 \end{array}$$

where age in years, BM = body mass (kg), H = height (cm), S = sex: male = 1, female = 0, and ICU0.75 = ICU correction factor of 0.75.

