### Inclusion and Exclusion Criteria

Participants will be patients of both sexes (18+ years) who have been mechanically ventilated for ≥7 days, consistent with the prior threshold for the development of ICU-AW [36], who voluntarily agree to participate, and have answered the self-reported functional ability questionnaire. Exclusion criteria will be defined as follows: those who self-report that they cannot climb at least one flight of stairs due to limited exercise capacity, have significant orthopedic or musculoskeletal impairment affecting mobility, have a medical history of neuromuscular disease, have ongoing respiratory limitations (ie, supplemental oxygen), have significant heart disease (ie, ejection fraction less than 30%, unstable ischemic heart disease, and severe valvular heart disease), have a BMI of ≥40 kg/m^2^ (impacting NIRS signal due to adipose tissue thickness) [37], or if the participant’s primary residence is a significant distance from the research center.

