##### $\dot{V}O_{2reserve}$ Calculation

$\dot{V}O_{2reserve}$ will be calculated as the difference between the estimated $\dot{V}O_{2peak}$ from Equation 1 and a fixed $\dot{V}O_{2rest}$ of 3.5 mL kg^−1^ min^−1^ (to promote efficiency within a clinical setting) to calculate $\dot{V}O_{2reserve}$ before participant arrival.

$\overset{˙}{V}O_{2reserve}=\overset{˙}{V}O_{2peak}-\overset{˙}{V}O_{2rest}$

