##### $\dot{V}O_{2CWR}$ Calculation

The target $\dot{V}O_{2CWR}$ will be determined as described in Equation 2, in which the $\dot{V}O_{2reserve}$ obtained in step 2, described above, will be multiplied by the desired intensity (30%).

(2)
$$\begin{array}{rl} \dot{V}O_{2CWR} & =\left[\left(\dot{V}O_{2\text{peak}}-\dot{V}O_{2\text{rest}})\times (\%\text{desired intensity}\right)\right]+\dot{V}O_{2\text{rest}} \end{array}$$

where $\dot{V}O_{2peak}$ (mL kg^−1^ min^−1^) is the value estimated in step 1 for ICU survivors; $\dot{V}O_{2rest}$ (mL kg^−1^ min^−1^) is the value of oxygen uptake at rest; and % desired intensity, expressed in decimals, is the desired intensity (relative to the individual’s $\dot{V}O_{2reserve}$) to perform the exercise. The 30% $\dot{V}O_{2reserve}$, a light intensity according to the American College of Sports Medicine [55], optimizes conditions so that participants perform the CWR exercise phase below the ventilatory threshold, to achieve a steady-state $\dot{V}O_{2}$ within 5 minutes, while minimizing interference with the subsequent progressive incremental phase of the protocol.

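### Equation 1 gives VO2peak in L/min by its size, but the next steps use it as mL/kg/min with no conversion; a lesser point is that it is stated for ages 40 and over while enrolment starts at 18

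*Protocol article*

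**What the plan says.** All references are to the protocol article.

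- **ICU Survivor Prediction Equation (Equation 1).** VO2peak is predicted from "a recent Canadian adult (≥40 years of age) normative (50th percentile) and sex-specific equation (Equation 1"). The inputs carry units: "where age in years, BM = body mass (kg), H = height (cm), S = sex: male = 1, female = 0". The result is scaled by "ICU0.75 = ICU correction factor of 0.75". No unit is given for the output.
- **VO2reserve Calculation.** The Equation 1 value is reduced by a fixed resting uptake "of 3.5 mL kg^−1^ min^−1^ (to promote efficiency within a clinical setting").
- **VO2CWR Calculation (Equation 2).** VO2peak is labelled mL/kg/min and "is the value estimated in step 1 for ICU survivors". The target is 30% of reserve plus the resting value.
- **Estimation of Work Rate in Watts (Equation 3).** The Equation 2 result enters in mL/kg/min together with body mass.
- **Inclusion and Exclusion Criteria.** "Participants will be patients of both sexes (18+ years) who have been mechanically ventilated for ≥7 days". No upper age limit is given.
- **Outcome Measures; Validation of ICU-Specific Protocol Adaptations; Statistical Analysis and Sample Size Calculation.** Agreement between predicted and measured VO2peak and VO2CWR is a secondary outcome. The 0.75 factor is judged on it, and the VO2peak agreement is the basis for 48 participants.

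**The concern.** The prescription is printed as a complete four-step calculation, with coefficients to nine decimals and a unit on each later term. The steps do not fit together. If the first step returns L/min, subtracting 3.5 mL/kg/min from it has no meaning, and the later steps inherit the fault. The predicted VO2peak is also one side of the agreement analysis, and Data Analysis reports it in mL/kg/min, so the missing step affects an outcome as well as the work rate. The article offers the method as a standard that other sites might adopt, and as printed it cannot be executed.

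The age range raises a smaller question. For participants aged 18 to 39 the linear age term is used outside the range the article gives for it. In those participants a gap between predicted and measured VO2peak could come from the 0.75 factor, from the extrapolation, or from both. The planned pooled analysis would not separate them.

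**Working it through.** **Inputs.** Coefficients, the 0.75 factor, resting uptake of 3.5 and intensity of 30% come from the article. The body sizes and ages are illustrative assumptions.

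**Formulas.**
- Eq 1: E = (0.012905699·H + 0.007291081·BM + 0.564188602·S − 0.016521850·A − 0.076072067) × 0.75
- Eq 2: VO2CWR = 0.30 × (E − 3.5) + 3.5
- Eq 3: W = BM × (VO2CWR − 7) / 1.8 × 0.164

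**The plan's own figure.** With δ/σ = 2.9, μ/σ = 0.2, two-sided α = 0.05 and 95% limits, the non-central t power calculation for Bland-Altman limits gives 80.7% at n = 46 and 82.5% at n = 48. The stated 48 is reproduced to within two participants. It depends only on ratios to σ, so the unit of VO2peak does not enter.

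**Step 1: size of Equation 1.** Over heights 150–200 cm, masses 45–140 kg, ages 18–85 and both sexes, E runs from 0.59 to 2.84. An extreme eligible case (man, 18 years, 210 cm, 176 kg, BMI just under 40) gives 4.184 × 0.75 = 3.14. All these values are below 3.5, and they are plausible only as L/min.

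**Step 2: man, 55 years, 175 cm, 80 kg.** E = (2.258 + 0.583 + 0.564 − 0.909 − 0.076) × 0.75 = 2.421 × 0.75 = 1.816.
- As printed: reserve = 1.816 − 3.5 = −1.68; VO2CWR = 0.30 × (−1.684) + 3.5 = 2.99; W = 80 × (2.995 − 7) / 1.8 × 0.164 = **−29.2 W**.
- Converted: 1.816 × 1000 / 80 = 22.7 mL/kg/min; VO2CWR = 0.30 × 19.2 + 3.5 = 9.26; W = 80 × 2.26 / 1.8 × 0.164 = **+16.5 W**.

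**Step 3: woman, 55 years, 162 cm, 70 kg.** E = 1.616 × 0.75 = 1.212.
- As printed: reserve −2.29, VO2CWR 2.81, **−26.7 W**.
- Converted: 17.3 mL/kg/min, VO2CWR 7.65, **+4.1 W**.

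**Step 4: when Equation 3 is positive.** It needs VO2CWR above 7, that is, a step 1 value above 3.5 + 3.5/0.30 = 15.2. The unconverted output never approaches this.

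**Step 5: age term.** From 40 down to 18 years it adds 22 × 0.016521850 × 0.75 = 0.27 L/min, which is 3.4 mL/kg/min at 80 kg and 3.9 at 70 kg. This is the whole change in the prediction at the youngest eligible age. It is not an estimate of error, and a 35-year-old is extrapolated by 5 years, not 22.

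**Step 6: how many might be under 40.** The article does not say. If age were normal, cut off at 18, with SD 14 and mean 50 to 60 (assumed), 23% to 8% would be under 40. That is 48 × 0.23 ≈ 11 down to 48 × 0.08 ≈ 4.

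**The case against.** The strongest reply is that the unit gap is a reporting slip. Equations 2 and 3 and Data Analysis all name mL/kg/min, so the intended scale is clear. A negative wattage cannot be set on an ergometer, so staff would notice at once. This stands, and it limits the consequence. A reader might infer that participants will exercise at wrong work rates, or that the validation will be run on wrong predictions. The documents do not support either inference. They show only that the algorithm as written is wrong. Nor can the gap be put down to an article's brevity, because every step is printed and the printed steps conflict.

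On age, a reader might take the 3 to 4 mL/kg/min shift at age 18 as bias. It is not. The prediction errs only so far as true VO2peak below 40 departs from the linear trend, and the documents say nothing on that, in size or direction. It is also fair to note that agreement is a secondary outcome, the primary being feasibility.

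Restricting the main analysis to ages 40 and over would be a poor remedy. On the assumed loss of 4 to 11 participants, power would fall from 82.5% to about 79% (n = 44) or 69% (n = 37). A different equation for younger participants would also change their prescribed work rate, not just the analysis.

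**Conclusion.** The unit error holds and needs correction: followed as printed, Equations 1 to 3 give a negative reserve and negative watts for essentially every eligible participant. That Equation 1 is in L/min is inferred from the size of its output, since no unit is stated, but no realistic adult gives a value usable as mL/kg/min. Once the conversion is made, neither 48 participants nor any planned outcome changes.

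The age mismatch is real but lesser. Predictions at ages 18 to 39 rest on extrapolation of up to 0.27 L/min after the 0.75 factor. The bias is unknown and so is the number of participants affected, and extrapolation error is mixed with error in the 0.75 factor.

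**What to change.** 1. State that Equation 1 returns L/min and print the conversion (x 1000 / body mass) before the reserve step.
2. Reconcile the four steps from Equation 1 to Equation 3. Conversion alone does not make every result usable: a woman of 70 years, 162 cm and 70 kg has a converted VO2peak of 14.7 mL/kg/min, below the 15.2 at which Equation 3 reaches zero, and gets −1.0 W. The authors need to resolve how these sections apply to such participants.
3. Keep all participants in the main predicted-versus-measured analysis. Pre-specify a sensitivity analysis restricted to age 40 and over, and report those aged 18 to 39 separately.

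Items 1 and 2 are changes to protocol text. Item 3 costs one extra, less precise analysis. It leaves the sample size, the eligibility criteria and the power of the main analysis as they are.

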##### $\dot{V}O_{2reserve}$ Calculation

$\dot{V}O_{2reserve}$ will be calculated as the difference between the estimated $\dot{V}O_{2peak}$ from Equation 1 and a fixed $\dot{V}O_{2rest}$ of 3.5 mL kg^−1^ min^−1^ (to promote efficiency within a clinical setting) to calculate $\dot{V}O_{2reserve}$ before participant arrival.

$\overset{˙}{V}O_{2reserve}=\overset{˙}{V}O_{2peak}-\overset{˙}{V}O_{2rest}$

##### $\dot{V}O_{2CWR}$ Calculation

The target $\dot{V}O_{2CWR}$ will be determined as described in Equation 2, in which the $\dot{V}O_{2reserve}$ obtained in step 2, described above, will be multiplied by the desired intensity (30%).

(2)
$$\begin{array}{rl} \dot{V}O_{2CWR} & =\left[\left(\dot{V}O_{2\text{peak}}-\dot{V}O_{2\text{rest}})\times (\%\text{desired intensity}\right)\right]+\dot{V}O_{2\text{rest}} \end{array}$$

where $\dot{V}O_{2peak}$ (mL kg^−1^ min^−1^) is the value estimated in step 1 for ICU survivors; $\dot{V}O_{2rest}$ (mL kg^−1^ min^−1^) is the value of oxygen uptake at rest; and % desired intensity, expressed in decimals, is the desired intensity (relative to the individual’s $\dot{V}O_{2reserve}$) to perform the exercise. The 30% $\dot{V}O_{2reserve}$, a light intensity according to the American College of Sports Medicine [55], optimizes conditions so that participants perform the CWR exercise phase below the ventilatory threshold, to achieve a steady-state $\dot{V}O_{2}$ within 5 minutes, while minimizing interference with the subsequent progressive incremental phase of the protocol.

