The cardiopulmonary exercise test (CPET) is used clinically and in research to assess aerobic fitness and exercise capacity, predict health outcomes, diagnose cardiopulmonary dysfunction and functional limitations, and evaluate response to interventions [7]. The most common exercise metric for CPET is peak oxygen uptake $(\dot{V}O_{2peak}$), defined as the highest $\dot{V}O_{2}$ achieved during a test [8], particularly until the limit of tolerance (or willingness), signifying exercise capacity within this protocol. For many healthy and diseased populations, $\dot{V}O_{2peak}$ is a robust and comprehensive evaluation of global cardiovascular fitness and a strong predictor of mortality [9-11]. Additionally, $\dot{V}O_{2}$ kinetics assess the integrated capacity of the O_2_ transport pathway [12]. $\dot{V}O_{2}$ on-kinetics refers to the exponential rise of $\dot{V}O_{2}$ toward a steady state from rest to exercise below the lactate threshold, where the slope of the exponential rise represents the rate at which oxidative phosphorylation adjusts to a sudden increase in energy demand at a constant workload, reflecting both systemic oxygen transport and muscle metabolism [13]. $\dot{V}O_{2}$ off-kinetics refers to the exponential decline of $\dot{V}O_{2}$ postexercise [12], representing the rate of metabolic recovery, where oxygen uptake returns to baseline levels. Moreover, faster $\dot{V}O_{2}$ kinetics constitutes a small O_2_ deficit, less substrate-level phosphorylation, and greater exercise tolerance, whereas slower $\dot{V}O_{2}$ kinetics is linked to a higher O_2_ deficit, presenting a greater challenge to homeostasis, and is associated with poor exercise tolerance [12]. Quantification of these 3 variables—$\dot{V}O_{2}$_peak_, $\dot{V}O_{2}$ on- and off-kinetics—is critical to understanding the interplay between cardiopulmonary and muscular physiological mechanisms [13,14]. Together, they contribute to the overall phenotype of aerobic fitness, exercise efficiency, and exertional tolerance that impact quality of life and overall survival [13,15-17].

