### Equipment

The ICU-CARE CPET protocol will be performed using an upright cycle ergometer (Lode Corival | CPET, Lode BV Medical Technology). The pulmonary oxygen uptake ($\dot{V}O_{2}$), carbon dioxide production ($\dot{V}{CO}_{2}$), and the respiratory exchange ratio of $\dot{V}{CO}_{2}$/$\dot{V}O_{2}$ will be collected, monitored, and reported mid-5 of 7 breaths averaged using the Ultima CardiO2 gas exchange analysis system metabolic cart (MGC Diagnostics). A fitted air-cushioned face mask (preVent) and a bidirectional breath-by-breath volume sensor (preVent) will be used to collect the ventilatory variables. The Ultima CardiO2 will be calibrated before each test by using automated gas and flow calibrations as well as quality assurance to ensure compliance with the procedures recommended by the ATS/ERS pulmonary function acceptability and repeatability guidelines, as described in the user manual. Heart rate will be recorded using a 12-lead Mortara electrocardiogram (ECG) embedded in the Ultima CardiO2 system [48]. Blood pressure will be recorded every 2 minutes using the Tango M2 Stress Test Monitor (SunTech Medical) system during the exercise test.

NIRS is a noninvasive optical technology that provides information on microvascular oxygen delivery and local tissue utilization in skeletal muscle during exercise [49,50]. This technology provides insight into the concentration and oxygenation of biological tissues through the status of light-absorbing chromophores, such as hemoglobin (Hb) and myoglobin (Mb) within the near-infrared region (700‐900 nm) penetrating several millimeters [25]. The NIRS device (PortaMon, Artinis Inc) will be placed on the vastus lateralis muscle [51-53], about 12‐14 cm above the knee, secured by a band to minimize motion artifacts during cycling exercise. Adipose tissue thickness will be measured over the vastus lateralis site using Sonosite PX Ultrasound System (FUJIFILM Sonosite, Inc).

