### Data Analysis

Similar to the $\dot{V}O_{2}$ analysis conducted on healthy adult populations [28], $\dot{V}O_{2}$ on-kinetics (rest-to-exercise transition), $\dot{V}O_{2peak}$, and $\dot{V}O_{2}$ off-kinetics (exercise-to-recovery transition) will be analyzed in the ICU-CARE CPET within a single bout—reporting the measured and predicted $\dot{V}O_{2peak}$ (mL kg^−1^ min^−1^), measured SS $\dot{V}O_{2}$ at CWR (mL kg^−1^ min^−1^), “actual” calculated 30% $\dot{V}O_{2reserve}$ (mL kg^−1^ min^−1^), and targeted intensity achieved at CWR as a percentage (%). Additionally, NIRS will be analyzed to evaluate skeletal muscle microvascular oxygenation. The primary variables will be pulmonary $\dot{V}O_{2}$, deoxyhemoglobin (HHb; deoxy[Hb+ Mb]), and TSI ($\frac{\left[oxy\left(Hb+Mb\right)\right]}{\left[oxy\left(Hb+Mb\right)\right]+\left[deoxy\left(Hb+Mb\right)\right]}*100$), measured noninvasively at a sample rate of 10 Hz.

Skeletal muscle oxygenation measured by NIRS (Portamon, Artinis Medical Systems) will be transmitted wirelessly into OxySoft software, time-synched with the metabolic cart with real-time impulse by inserting key commands on the NIRS computer (listed in Figure 1). On OxySoft, export NIRS data to Microsoft Excel, then adjust to timestamps as described above and illustrated in Figure 2. For a combined analysis, $\dot{V}O_{2}$ and NIRS data will be preprocessed using a customized LabVIEW code (LabView v20.0.01, National Instruments Corp), specifically designed to perform the required analyses. The first analysis removes noise and motion artifacts. Initially, outliers will be removed by applying 2 standard deviations in a window size of 7 seconds, then applying a 350-second moving average, linearly interpolated to provide second-by-second values [52]. Then, the data is resampled at 1 Hz and time-aligned with each transition to be synchronized with the metabolic cart.

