With exercise starting at zero, subsequent analysis will be performed using a mono-exponential model to fit the pulmonary or primary component of the $\dot{V}O_{2}$ response (ie, phase II) by skipping the cardiogenic phase (ie, phase I), as previously recommended [33,58], left-shifting at 20 s in length [52]. Then, the steady-state $\dot{V}O_{2}$ (SS $\dot{V}O_{2}$ or phase III) will be calculated as the average of the last 2 minutes of the CWR exercise phase [28]. The mono-exponential fitting is characterized by $\dot{V}O_{2}$ parameters, including tau (τ), time delay (TD), amplitude A_0_ and A_1_, and mean response time (MRT), where τ is defined as the time constant of the exponential function, representing the time taken to reach 63% of the steady-state or final value; TD records the delay to the exponential response start (ie, phase II) (the model is not constrained to pass through the origin) before oxygen uptake responds to exercise; A_0_ represents the baseline value (resting $\dot{V}O_{2}$), whereas A_1_ represents the change of amplitude from baseline to steady-state $\dot{V}O_{2}$ (ie, SS $\dot{V}O_{2}$ – baseline value); and MRT, defined as TD + τ, representing the overall time to adjust the rate of $\dot{V}O_{2}$ to changes in workload [28]. At the end of the incremental phase, $\dot{V}O_{2peak}$ will be defined as the highest value of the last 30 seconds before volitional exhaustion after applying a 20-second moving average [59,60]. The quality of the fitting will follow our previous protocol [28]. The analysis of residuals, the degree of linear correlation between the experimental data and fitted function (*r*), the 95% CI band, and the significance level (*P* value) of the estimated parameters are used to determine the quality of the fitting.

The HHb signal will be normalized using a 60-second average before the exercise begins, then analyzed by detecting the nadir, occurring after a sudden decrease in HHb signal, to exclude data not associated with muscular $\dot{V}O_{2}$ dynamics, referring to the muscle pump [61]. After the nadir, HHb increases monoexponentially, representing the $\dot{V}O_{2}$ dynamics during the onset of exercise [27,62-64].

The HHb monoexponential function is expressed in the equation below:

$$HHb\;{\left(t\right)}^{\;}=HHb_{bl}+a\left[1-e^{-\left(t-TD\right)/\tau }\right]$$

where HHb_bl_=HHb baseline, *a*=amplitude, *e*=mathematical constant, *t*=time, TD=time delay, and τ=time constant.

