MRT of the HHb is also estimated by the sum of τ and TD, to determine the MRT time constant.

Changes in TSI will be assessed by calculating the difference between baseline (average 30 seconds before CWR) and end of exercise (30-second average before start of recovery) to quantitatively evaluate tissue saturation fluctuation of oxygen uptake within the skeletal muscle, reported as ΔTSI [%] in the equation below:

$$\Delta TSI\;\left[\%\right]={TSI}_{peak}-{TSI}_{bl}$$

where TSI_peak_=30-second average before $\dot{V}O_{2peak}$; TSI_bl_=TSI baseline, 30-second average before commencing exercise.

Secondary variables from the CPET will be collected in an exploratory manner. These include carbon dioxide output ($\dot{V}{CO}_{2})$, respiratory exchange ratio, oxyhemoglobin, heart rate response, peak oxygen pulse, tidal volume, breathing frequency, minute ventilation (VE), ventilatory efficiency (VE/VCO_2_), and breathing reserve. Measured adipose tissue thickness of ≥12.5 mm will define a subgroup of patients with less reliable skeletal muscle NIRS measurements [37]; sensitivity analysis will be undertaken with both inclusion and exclusion of this subgroup in cohort outcomes. Other variables to consider include the CPET time of completion, patient-reported outcomes, and any other additional comments regarding the ICU-CARE CPET protocol experience.

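### The constant-work-rate load is justified as staying below the ventilatory threshold, but the stated analysis reports only achieved intensity and so cannot show who crossed it

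*Protocol article*

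**What the plan says.** All references are to the protocol article.

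- **Introduction.** On-kinetics is the exponential rise in oxygen uptake "toward a steady state from rest to exercise below the lactate threshold".
- **VO2CWR Calculation.** The 30% intensity is chosen because it "optimizes conditions so that participants perform the CWR exercise phase below the ventilatory threshold" and lets steady state be reached within 5 minutes.
- **ICU Survivor Prediction Equation for VO2peak.** The reserve comes from a normative equation times 0.75, a factor that "is to be multiplied based on an average of 25" percent reduction in survivors. Validation of ICU-Specific Protocol Adaptations treats that factor as still to be tested.
- **VO2reserve Calculation.** Resting uptake is fixed at 3.5 mL/kg/min.
- **Data Analysis.** Outputs include measured and predicted peak, measured steady-state uptake and "targeted intensity achieved at CWR as a percentage". For kinetics, "subsequent analysis will be performed using a mono-exponential model to fit the pulmonary or primary component of the" oxygen-uptake response. Steady state is the mean of the last 2 minutes of the CWR phase. Fit quality is judged thus: "The analysis of residuals, the degree of linear correlation between the experimental data and fitted function", together with the 95% CI band and parameter P values. "Secondary variables from the CPET will be collected in an exploratory manner"; the list includes carbon dioxide output, minute ventilation and ventilatory efficiency.
- **Equipment.** The gas-exchange signals are recorded throughout the test and "will be collected, monitored, and reported mid-5 of 7 breaths averaged".

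No part of the stated analysis derives a ventilatory threshold or makes a kinetics result depend on one.

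**The concern.** The protocol gives a condition under which its time constant has the intended meaning, namely exercise below threshold. It then sets the load from a population average. Anyone whose true peak is below the estimate works above 30% of true reserve, and some of them may be above threshold. Achieved intensity shows relative load, but two people at the same percentage of reserve can lie on opposite sides of their own thresholds.

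Above threshold, uptake may keep rising instead of levelling off within 5 minutes. A single mono-exponential fitted through a continuing rise returns a longer tau. This error would not be random, because the people most likely to be overloaded are those with the lowest peak relative to prediction. It could therefore create an association between low peak and slow kinetics. Evaluation of Exercise Capacity in ICU Survivors proposes to use relationships of that kind to describe mechanisms of ICU-acquired weakness.

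**Working it through.** **Inputs from the article:** Equation 1 (read as L/min), factor 0.75, rest 3.5 mL/kg/min, intensity 30%, and the 80-85% of predicted peak cited in Rationale for Protocol Development.

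**Assumed:** the participant profiles; true peak as a fraction f of normative outside 75-85%; the threshold as a share of measured peak (50%, range 40-60%); the size and shape of the drift; and uptake at the CWR equal to its target.

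**Step 1. Reproduce the target.** Man aged 60, 175 cm, 80 kg:

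- Normative peak = 0.012905699×175 + 0.007291081×80 + 0.564188602 − 0.016521850×60 − 0.076072067 = 2.339 L/min; ×1000/80 = 29.23 mL/kg/min.
- Estimated peak = 0.75×29.23 = 21.92.
- CWR target = 0.30×(21.92 − 3.5) + 3.5 = 9.03.

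Woman aged 60, 162 cm, 65 kg: normative 23.03, estimated 17.28, CWR target 7.63.

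**Step 2. Relative load if true peak is f × normative (man).** Share of reserve = (9.03 − 3.5)/(f×29.23 − 3.5). Share of peak = 9.03/(f×29.23).

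| f | % of true reserve | % of measured peak |
|---|---|---|
| 1.00 | 21.5 | 30.9 |
| 0.85 | 25.9 | 36.3 |
| 0.80 | 27.8 | 38.6 |
| 0.75 | 30.0 | 41.2 |
| 0.60 | 39.4 | 51.5 |
| 0.50 | 49.7 | 61.8 |

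For the woman, f = 0.60 gives 40.0% of reserve and 55.2% of peak; f = 0.50 gives 51.5% and 66.3%.

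Grid: men 175 cm, 70-90 kg; women 162 cm, 55-75 kg; ages 40-80 in 5-year steps; the 78 of 90 profiles for which Equation 3 gives positive watts.

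- f = 0.60: 38.9-40.5% of reserve, 48.5-57.4% of peak.
- f = 0.50: 48.5-52.8% of reserve, 58.2-68.9% of peak.

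**Step 3. Break-even.** The threshold is crossed when f falls below CWR target/(threshold share × normative peak).

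- Man, threshold at 50% of peak: 9.03/(0.50×29.23) = 0.62. At 40%: 0.77. At 60%: 0.51.
- Woman, threshold at 50% of peak: 7.63/(0.50×23.03) = 0.66. At 40%: 0.83. At 60%: 0.55.

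**Step 4. Effect on tau.** Noise-free mono-exponential, amplitude 5.53 (9.03 − 3.5), tau/delay 40/10 s and 60/15 s, plus a linear drift starting at 90, 120 or 150 s and reaching 5% or 10% of amplitude at 300 s. The response is refitted from 20 s to the stated end-point.

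| Fit window | Tau, 5% drift | Tau, 10% drift |
|---|---|---|
| 20-300 s | +11 to 14% | +23 to 32% |
| 20-180 s | about +1.5 to 6.5% | about +3 to 13.5% |

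Over 20-300 s, r stays at or above 0.995. With tau 40, delay 10 and onset 120 s, fitted tau is 45.7 s (r 0.9991) at 5% drift and 52.7 s (r 0.9971) at 10%. With baseline fixed at 3.5, mean response time over the same window rises by 6-8% and 15-17%.

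The 180 s end-point is a fair alternative because the article fits the primary component and computes steady state separately from the last 2 minutes (180-300 s). It does not say which end-point applies.

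**The case against.** The case against has real force.

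- **A condensed article.** Reading a threshold from the ramp and defining a sensitivity subset are typical analysis-plan content, the CPET variable list is not closed, and fit quality follows an earlier protocol not at hand. This stands: the article cannot be said to rule out a threshold analysis. But it describes the kinetics analysis in detail, and nothing there depends on the condition used to justify the load.
- **The sentence on 30% is not wrong.** It explains why a light intensity was chosen and guarantees nothing for an individual. This stands; there is no contradiction.
- **Partial checks exist.** Achieved intensity identifies who worked well above 30%, and residuals or CI bands might reveal misfit. This stands in part. The calculation shows only that r would not flag the drift; residuals and CI bands were not tested. The article states no rule for acting on any of these checks, and none locates a threshold.
- **The size is assumed.** At 75-85% of normative the load is on or under target. The stairs, oxygen and heart-disease exclusions and the exclusion of mMRC grade 4 trim the low tail. No document links crossing the threshold to a 5-10% drift. All of this stands.
- **Low stakes.** Further secondary testing is labelled hypothesis generating. This also stands.

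A reader might infer that a large share of participants will exceed threshold. One illustration gives about 12-40%, but it assumes an estimated peak of 15-22 mL/kg/min, prediction-error CVs of 15-30% and a threshold at 50% of peak. The article gives neither error CVs nor threshold values, so it supports no such share.

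**Conclusion.** The point holds as a modest one. The protocol's own premise for interpreting on-kinetics is not tested for each participant in the stated analysis, and achieved percentage of reserve does not replace that test.

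On the article's own 75-85% of normative peak, the example man is at 26-30% of reserve. Being on target for reserve is still not proof of being below threshold: at f = 0.75 he is at 41.2% of peak, which exceeds a threshold at the low end of the assumed range (40%). With the threshold at 50% of peak, the risk is confined to those below about 62-66% of normative in the two example profiles. There, tau could be lengthened by roughly 1.5-32%, given the assumed drift and its onset and a fit end-point between 180 and 300 s.

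The documents do not support two stronger readings: that the 30% load is wrongly set, or that the tau estimates will be invalid for the cohort. The primary feasibility outcome is unaffected.

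**What to change.** Leave the exercise test as it is and add to Data Analysis:

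1. Derive each participant's ventilatory threshold from the gas exchange of the same session's ramp.
2. Classify measured steady-state CWR uptake as below threshold, above threshold or indeterminate.
3. Keep everyone in the main kinetics report, and show the class beside the achieved percentage of measured reserve.
4. Prespecify a sensitivity analysis of tau, mean response time and deoxyhemoglobin kinetics limited to participants classified as below threshold. Complete it before slow kinetics are read as impaired oxygen transport or muscle metabolism.

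**Cost:** extra analysis of signals already recorded, with no added testing or participants. Some thresholds will be indeterminate, possibly in the least fit, including people already above threshold when the ramp starts. The check is therefore weakest where the concern is greatest. The sensitivity set will also be smaller than the full cohort.
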